### Outcomes {12}

#### Primary outcomes

The implementation outcomes would be studied next using the evaluation framework developed by Procter et al. for implementation outcomes that will be applied including acceptability, adoption (uptake), appropriateness, costs, feasibility, fidelity, penetration (integration of a practice within a specific setting), and sustainability.

For the digital m-health platform, our intervention will be monitored by the non-adoption, abandonment, scale-up, spread, and sustainability (NASSS) framework that is applicable across a range of technological innovations in health and social care. The proposal helps implementation of WHO-PEN protocol for self-care guidelines including utilising frontline health workers in improving self-care in patients of CMM, counselling to improving adherence and self-care, and considering patients’ beliefs and concerns about drugs and their effect.

Details of the other patient-reported outcome measures are given in Table 2.

**Table 2 Tab2:** Outcome measurement tools

Objective	Variable/Outcome	Measurement tool
Acceptability/Adoption/appropriateness	Qualitative measures- Changes in perception at the level of stakeholders, participants, frontline health workers, LSG leaders Increased footfalls in the public health system (PHC, CHCs) Increased demand for drugs targeting CMM at the PHCs, CHCs, Taluk hospital of the study area	FGD Guide, In Depth Interview Guide, Pre-post audit of demand for drugs for hypertension and number of individuals following up with the public health system
Penetration	Inclusion of improving adherence to the state NCD program charter	
Fidelity	Whether participants were following intended toolkit as per instructions	Check lists, Meeting reports
Cost effectiveness	Incremental cost for an improvement in HbA1c by 0.5%	Cost of implementation
Effectiveness	Effectiveness of the lifestyle toolkit in control of disease parameters	FFQ, WHO ASSIST, MMAS-8, PSS-10, EQ- 5D -3L, BP, HbA1c, BMI measurements

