#### Research question

How can a co-developed, context-specific lifestyle toolkit achieve high coverage and equitable adoption of lifestyle practices for managing CVD among individuals with CMM in a community setting, using the WHO-HEARTS framework?

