### Trial setting {9}

The study is to be carried out in the ENDIRA cohort of Ernakulam, Kerala [22, 23]. The ENDIRA (‘Epidemiology of Non-communicable Diseases In Rural Areas’) cohort (*n* = 114,064) includes all individuals from five panchayats (villages) in Ernakulam district, Kerala. Four of the five panchayats have family health centres (FHCs), and one community health centre (CHC), which are further divided into 18 sub-centres and 75 wards having 2064 individuals with documented cardiovascular diseases. Among these individuals, 37.3% were diabetic, 53.5% hypertensive, 30.5% were dyslipidaemic, 16.8% were tobacco users, and 23.2% were alcohol users [24]. Leveraging previous research initiatives in this region ensures the seamless integration of the current study and enhances its generalisability to a broader context.

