### Strategies to improve adherence to intervention/comparator protocols

For diet and nutrition, a Food Frequency Questionnaire would be administered at 0, 6, and 12 months. Additionally, participants would be requested to send a photograph of their food plate for calorie assessment (using the CalAI App) on three different occasions during the study period.

For physical activity, participants are encouraged to maintain log books of physical activity in minutes per day, and if available to use a step-counter to measure the number of steps per day.

For stress management, yoga sessions would be conducted online in the JAKs. A yoga trainer would schedule yoga sessions in one of the JAK centres with participants for that centre being guided in-person, while the other eight JAK centres join online for the session with participants encouraged to join from individual JAK centres. Nine such sessions of breathing exercises, postures, and mild stretching exercises are planned, one in each of the JAK centres, for the 9 weeks. The digital platform for the same has been created to facilitate the process.

For tobacco and alcohol cessation, counselling would be based on the WHO-ASSIST scores and planned accordingly with expert opinion sought in those needing the same.

For improving adherence to medications, a mix of digital prompts, tunes and jingles at weekly intervals for 4 weeks, and monthly for the next 9 months is planned as reminders to adherence and on the benefits of the same.

The intervention as envisaged is anchored in the public health system through the JAKs, with the interventions to be carried out by the JAK staff enabled and facilitated in all aspects by digital technology and a m-health platform.

In addition, each of the participants from the intervention arm has a password-encrypted access to the Shraddha app and portal which gives them access to health modules on lifestyle modifications. Participants are also given the liberty to upload health details like laboratory tests (sugar, glycated haemoglobin, etc.), or reach out with specific queries which would be addressed online in 24 h. The two-way app, to our mind, ensures ownership, participation, and would help curb dropouts.

Our previous experiences in the cohort using frontline health workers and digital platforms in the same cohort encourage us to utilise the same [34–36].

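### Adoption is a declared primary outcome, but its only countable indicators are facility- or area-level proxies that respond weakly to uptake of the toolkit

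*Protocol article*

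**What the plan says.** Under Outcomes {12}, Primary outcomes, the protocol article names eight implementation outcomes: "acceptability, adoption (uptake), appropriateness, costs, feasibility, fidelity, penetration (integration of a practice within a specific setting), and sustainability". The Sample size section confirms that implementation outcomes are the main focus of the trial. The Research question asks how the toolkit can "achieve high coverage and equitable adoption of lifestyle practices" among individuals with CMM.

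Table 2 gives acceptability, adoption and appropriateness a single row with three variables:

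- "Qualitative measures- Changes in perception at the level of stakeholders, participants, frontline health workers, LSG leaders", collected with focus group and interview guides;
- "Increased footfalls in the public health system (PHC, CHCs";
- "Increased demand for drugs targeting CMM at the PHCs, CHCs, Taluk hospital of the study area".

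The tool for the last two is a before-and-after audit of hypertension-drug demand and of how many people follow up in the public system. Table 3 gives only qualitative measures for the same row.

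Delivery takes place elsewhere. According to the sections on eligibility of sites and on strategies to improve adherence, JAK sub-centre staff deliver the toolkit. Yoga sessions are held at the nine intervention JAKs, and "each of the participants from the intervention arm has a password-encrypted access to the Shraddha app and portal".

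**The concern.** Adoption in the sense of uptake asks how many of the people and centres offered the toolkit took it up. Neither countable variable in the row answers that. Footfall counts people attending primary and community health centres. Drug demand counts supply at those centres and at the Taluk hospital. Either can rise without any use of the toolkit, for example through better drug supply or another programme. Drug demand is at best linked to one of the toolkit's five components, medication adherence.

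The protocol's own analysis is affected. Statistical analysis {20a} plans panel regression of the quantitative implementation measures, to show how implementation success varies across sites, with benchmarks set before the start. A facility total cannot be assigned to a JAK, and it does not show whether uptake was equitable across participants. A primary outcome could then be reported as met or not met on a number that depends mainly on other things.

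**Working it through.** **The plan's own figure.** The documents give no figure for adoption. The HbA1c sample size reproduces: 142 per arm under individual randomisation; design effect 1 + 89 × 0.05 = 5.45; 142 × 5.45 = 773.9, rounded up to 774; planned 9 × 90 = 810 per arm. This point does not affect it.

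**Inputs from the documents.** Area population 114,064 (Trial setting {9}; the cohort "includes all individuals from five panchayats (villages) in Ernakulam district, Kerala"). Arm A 810 (Sample size {14}). Four family health centres and one community health centre above 18 sub-centres (Trial setting). Nine sub-centres per arm (Study implementation).

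**Inputs assumed.** No visit volumes are given. Let k be the visit rate of arm A members relative to other residents, from 1 to 10. Suppose every arm A member takes up the toolkit and makes 20% or 50% more visits.

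**Footfall.** Arm A share of the population: 810/114,064 = 0.71%. Share of footfall = 810k/(113,254 + 810k). Rise in total footfall = share × relative increase in visits.

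| k | Share of footfall | Rise if visits +20% | Rise if visits +50% |
|---|---|---|---|
| 1 | 0.71% | 0.14% | 0.36% |
| 5 | 3.5% | 0.69% | 1.7% |
| 10 | 6.7% | 1.3% | 3.3% |

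If both arms are frequent attenders, the share is 810k/(1,620k + 112,444). This gives 0.71%, 3.4% and 6.3%, and a 20% increase then moves the total by 0.14%, 0.67% and 1.3%. The conclusion is unchanged. On the same contrast, a direct measure in arm A would run from 0/810 to 810/810.

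**Drug demand.** Suppose 5,000 to 20,000 people in the area are supplied with hypertension drugs (assumed). Arm A is then 810/5,000 = 16.2% to 810/20,000 = 4.05% of them, and a 20% increase moves demand by 3.2% to 0.8%.

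**Restricted list.** If the audit followed only the 2,064 people with documented cardiovascular disease, and all 810 were among them, arm A would be 810/2,064 = 39% and a 20% increase would show as 7.8%. This is an upper case, because diabetes plus hypertension qualifies for the trial without documented cardiovascular disease.

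**Level of measurement.** Eighteen sub-centres under five facilities is 3.6 per facility. With nine sub-centres per arm, the chance that all k′ sub-centres of one facility fall in the same arm is 2 × C(9,k′)/C(18,k′): 168/816 = 21% for three, 252/3,060 = 8% for four, 252/8,568 = 3% for five. Most facility counts would therefore mix the two arms.

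**The case against.** The strongest reply is that the trial does look at use. The shared row puts qualitative perception change first, and interviews with users and staff would differ between a toolkit that is ignored and one that is used. The Fidelity row records, by checklists and meeting reports, whether participants follow the toolkit. The NASSS framework is named for monitoring the digital platform, including its non-adoption. Monthly reviews and quality checks are planned. Diet, physical activity, substance use and medication adherence are measured per participant at baseline, 6 and 12 months, which bears directly on the lifestyle practices named in the research question.

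All of this stands, and it limits the point. A reader might infer that the trial could not tell an unused toolkit from a widely used one, or that a null HbA1c result could not be interpreted. The documents do not support either inference, because non-use should show through these other channels. Nor is adoption measured by footfall and drug demand alone. What remains is that none of these channels is tied to adoption, and none is stated to yield the proportion of people or centres that took the toolkit up.

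A second reply is that the percentages rest on assumed visit rates, and that coverage of the whole area is explicit only for drug demand and inferred for footfall. That is correct: the figures are illustrative, and the restricted-list case shows how far they could move.

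A third reply is that log-in metrics and thresholds belong in a fuller document. Thresholds may. But Table 2 already fixes the variables and the tool, and a fuller analysis plan for footfall would still not measure uptake of the toolkit.

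**Conclusion.** The point holds in a limited form. The only countable adoption indicators are facility- or area-level proxies with no stated restriction to participants or arm A. They are taken at a different level from the delivery of the toolkit, and they respond weakly to uptake. With visit rates 1 to 10 times those of other residents and a 20% increase by all of arm A, total footfall would move by about 0.14% to 1.3%. The weak response is clearest for total footfall and less marked for hypertension-drug demand (about 0.8% to 3.2% under the assumed supply) or a restricted patient list (up to 7.8%). The mismatch between indicator and construct does not depend on these assumptions, as it can be read from Table 2. This is a worthwhile and cheap correction to how a primary outcome is defined. It does not threaten the effectiveness comparison.

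**What to change.** Split the shared row in Table 2 and give adoption its own definition:

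- Participant level: the proportion of eligible people in the nine intervention JAK areas who use the toolkit, taken from app or portal accounts or from attendance at JAK or yoga sessions, at 6 and 12 months.
- Provider level: the proportion of intervention JAKs, or of JAK staff, delivering it.

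Set the threshold for use before the start, alongside the benchmarks that the Statistical analysis section already promises. Say how the Fidelity and NASSS data relate to this measure. Keep footfall and drug demand as secondary system-level descriptors, and state whom the audit counts. Align Table 3.

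The cost is a change of wording, an export of platform use data and the keeping of attendance lists. App data alone would miss people reached only in person, which is why the definition accepts either app use or attendance. In return, the planned across-site analysis would have a measure that can be assigned to each JAK.

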#### Measurements

Blood sugar and HbA1c would be assessed with self-calibrated point-of-care (POC) devices, and weight and height with digital scales and stadiometers. The above would be measured at baseline and endline and one time-point of 6 months in between using standard procedure. Details of the other patient-reported outcome measures are given in Table 2.

### Data collection methods {18a}

Data will be collected at household (demographic data, data collected using standardised tools/questionnaires), by ASHA workers, and will be entered into a tablet PC. Before starting data collection, all research staff will be trained in the protection of human subjects, good clinical practice guidelines and administration, data entry, and analysis of study-specific data collection tools.

### Plans to promote participant retention and complete follow-up, including list of any outcome data to be collected for participants who discontinue or deviate from intervention protocols {18b}

All efforts will be made to retain all participants in the study. As they are also part of the earlier community awareness and intervention study, there is a good rapport with the study group, local self-government, and frontline health workers.

### Data management {19}

All the data collectors and research team members associated with field implementation will receive refresher training at regular intervals to ensure data quality and adherence to the intervention protocol. Monthly review and facilitation meetings will be organised at the village level to retain the participants in the intervention arm. Written informed consent will be sought from all participants. A thumb impression and signature of the witness will be taken for illiterate participants.

### Data monitoring committee {21a}

The data would be managed by the PI and the statisticians at the study centre.

### Frequency and procedures for monitoring trial conduct. If there is no monitoring, give explanation

Monthly review and facilitation meetings at ward level, refresher training, monthly quality assurance checks; the study team will oversee field implementation.

### Explanation of any interim analyses and stopping guidelines, including who will have access to these interim results and make the final decision to terminate the trial {21b}

Being a behavioural intervention, it will take 1 year for intervention, so an interim analysis is not being considered.

### Auditing {23}

Not applicable. No independent auditing is planned due to the low-risk, non-pharmacological nature of the intervention.

#### Study duration and follow-up

The study will be of 24 months including 12 months of intervention, and outcomes will be measured at baseline 6 and 12 months for primary and secondary outcomes.

### Explanation for choice of comparator {6b}

#### Study implementation

Each sub-centre (JAK) serves as a cluster and is randomised to either the intervention (lifestyle toolkit) delivered by JAK staff (JHI, MLSP, JPHN), leveraging a digital health platform (arm A) or control arm standard of care (SoC) (arm B), by listing all the sub-centres and then using random number table for randomisation to nine clusters per arm. Each individual identified with CMM in the cluster is then consented to the study (Fig. 1).

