### Mechanism used to implement the random allocation sequence {16b}

Since randomisation is at cluster level, allocation will be revealed at cluster assignment.

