### Whether the personnel who will enrol and those who will assign participants to the interventions will have access to the random allocation sequence {16c}

The allocation sequence will be generated by the statistician; frontline health workers will enrol participants at household level using questionnaires on a tablet PC; randomisation is at cluster (sub-centre) level and interventions delivered at sub-centre by Janakeeya Arogya Kendra (JAK) staff which includes junior health inspectors (JHI), mid-level service provider (MLSP), and junior public health nurses (JPHN).

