### Participant timeline {13}

**Table Tabb:** 

Timepoint	Trial period				
	Enrolment		Post-randomisation		Close-out
	(−ti to 0)	0	t1 (6 mo)	t2 (12 mo)	tx
Enrolment					
Eligibility screen	X				
Informed consent	X				
Baseline demographics	X				
Cluster randomisation (sub-centres: arm A/arm B)		X			
Intervention/comparator					
Shraddha lifestyle toolkit (arm A)		X			X
Standard of care (arm B)		X	X	X	X
Assessments					
Clinical measures (BP, weight, BMI)	X		X	X	X
Laboratory (HbA1c)	X		X	X	X
Diet (FFQ/calorie tracking)	X		X	X	X
Physical activity (GPAQ)	X		X	X	X
Substance use (WHO-ASSIST)	X		X	X	X
Medication adherence (MMAS-8)	X		X	X	X
Mental stress (PSS-10)	X		X	X	X
Quality of life (EQ-5D-L3)	X		X	X	X
Implementation outcomes (acceptability, adoption, appropriateness, fidelity, cost effectiveness)			X	X	X

Baseline = 0; t1 = 6 months (midline); t2 = 12 months (endline). The arrow indicates continuous delivery of the Shraddha lifestyle toolkit (mHealth messages, JAK visits, yoga sessions) from allocation to endline. Protocol v4 (26 September 2025); IEC ASM-AIMS ECASM-AIMS-2024-001; CTRI/2025/08/092529

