### Who will obtain informed consent or assent from potential trial participants or authorised proxies, and how {26a}

Informed consent will be taken by the accredited social health activist (ASHA) of the area who will be collecting the data. The data collection will be through an application called SHRADDHA installed in tablet PCs provided to them. The participant’s digital signature will be obtained on the tablet.

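### The implementation text consents people after their sub-centre is randomised, while the schedule puts consent first; following the text lets entry depend on a known arm

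*Protocol article*

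**What the plan says.** All references are to the protocol article.

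**Order of events.** Study implementation, under Explanation for choice of comparator {6b}, assigns sub-centres to arms "by listing all the sub-centres and then using random number table for randomisation to nine clusters per arm". The next sentence reads "Each individual identified with CMM in the cluster is then consented to the study". The Participant timeline {13} marks the rows for eligibility screen, "Informed consent" and baseline demographics only in the enrolment column (−ti to 0). The row "Cluster randomisation (sub-centres: arm A/arm B" is marked at 0.

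**Knowledge of allocation.** Section {16b} says: "Since randomisation is at cluster level, allocation will be revealed at cluster assignment". Section {17a} calls the trial non-blinded, lists participants and intervention staff as aware, and blinds only the analysts.

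**Who recruits.** Section {16c} says "frontline health workers will enrol participants at household level using questionnaires on a tablet PC". Section {26a} says: "Informed consent will be taken by the accredited social health activist (ASHA) of the area who will be collecting the data". The Health Belief Model text under Patient and public involvement also has ASHAs give support during home visits.

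**Who is analysed.** Consent and agreement to follow-up are inclusion criteria in {10}. Eligible individuals are then analysed by the allocation of their cluster, under intention to treat.

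**Retention.** Data management {19} says: "Monthly review and facilitation meetings will be organised at the village level to retain the participants in the intervention arm". Section {18b} promises efforts to keep all participants, and the section on monitoring trial conduct describes monthly ward-level meetings without naming an arm.

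**The concern.** Cluster randomisation makes the clusters comparable in expectation. It makes the enrolled individuals comparable only if entry does not depend on the arm. When a recruiter and a prospective participant both know whether the sub-centre will offer an app, yoga sessions and counselling or usual care, two things can differ by arm: who agrees to take part, and how the exclusions that need judgement are applied. Two exclusions in {10} leave such room: cognitive impairment that prevents a person from following instructions, and an open-ended category of other confounding illness.

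What is at stake is the between-arm comparison of HbA1c, blood pressure, BMI and adherence. If the arms contain different kinds of people at entry, part of any difference at 12 months reflects recruitment and not the toolkit. A similar question arises later if effort to keep people in follow-up differs by arm.

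**Working it through.** The core check is a comparison of sections. Arithmetic serves only to ask whether a size can be attached.

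**1. Do the two orders conflict?**

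| Step | Study implementation | Participant timeline {13} |
|---|---|---|
| First | Sub-centres listed and randomised, nine per arm | Screening, consent, baseline (−ti to 0) |
| Second | Individuals with CMM consented | Cluster randomisation (0) |

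They conflict. This is two incompatible statements, not a detail left to another document.

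**2. Does anything else settle the order?** No. Section {16b} only says that allocation becomes known at assignment. That fits either order. It matters because, if assignment comes first, nothing is concealed during recruitment.

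**3. If Study implementation is followed, is recruitment protected?** No section says that recruiters or prospective participants stay unaware of the arm until consent. Participants are stated to be aware. ASHAs are not named among those aware, but only analysts are blinded and ASHAs support the intervention, so their knowledge is a reasonable inference.

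**4. Does intention to treat repair it?** No. It keeps enrolled people in their cluster's arm. Consent is an entry condition, so anyone who refuses or is judged ineligible is absent from the analysed set.

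**5. Can the size be derived?** The plan's own figures reproduce. For a 0.5-point HbA1c difference, SD 1.5, 80% power and two-sided alpha 0.05, the number is 142 per arm. The design effect is 1 + (90 − 1) × 0.05 = 5.45, and 142 × 5.45 = 773.9, rounded up to 774. With 810 per arm:

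SE of the arm difference = 1.5 × √(2 × 5.45 / 810) = 0.174 points.

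Let *d* be the difference between arms in the share of participants from some subgroup, and *g* that subgroup's difference in mean HbA1c. The bias is *d* × *g*. Neither value is in the document. Over an assumed range:

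- *d* = 0.05, *g* = 0.5: bias 0.025 points, 5% of the 0.5 target.
- *d* = 0.20, *g* = 1.5: bias 0.30 points, 60% of the target.

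In an endline comparison that ignores baseline, the false-positive rate, Φ(bias/SE − 1.96) + Φ(−bias/SE − 1.96), would run from about 5.2% to 41%. That is not the planned analysis: {20a} specifies a multilevel repeated-measures model with individual covariates, which would absorb part of an HbA1c imbalance. The range runs from trivial to serious depending on inputs that nobody has, so no size can be stated.

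**The case against.** The strongest reply is that there is little room for selection. Section {15} aims to enrol all eligible people in each cluster, Study implementation itself speaks of each identified individual, and Rationale for selection says that people with CMM are already identified in ENDIRA. No section has an ASHA choosing among candidates. HbA1c is measured after consent, so a recruiter could select only on its correlates. Baseline values are collected and the planned model adjusts for covariates. Implementation outcomes are primary, and HbA1c is an additional effectiveness outcome. All of this stands and lowers the risk. It does not remove differential refusal, exclusions made by judgement, or differences in unmeasured traits such as motivation.

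Three stronger readings are tempting and are not supported.

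- **That about 22% of candidates would be left out at the recruiter's discretion.** A reader might take 2064 / 18 = 114.7 per sub-centre against 90 enrolled. But the 2064 in Trial setting {9} have documented cardiovascular disease; they are not a count of people eligible under {10}. If fewer than 1620 / 2064 = 78.5% qualify, nobody on that list is surplus. Assume each has one other qualifying condition, and that diabetes (37.3%) and hypertension (53.5%) overlap independently: 1 − 0.627 × 0.465 = 70.8%, or about 81 per sub-centre before exclusions. Conversely, people with diabetes and hypertension but no cardiovascular disease also qualify, so the pool could be larger.
- **That the false-positive rate is materially inflated by a known amount.** Any such figure needs assumed inputs, and the illustrated rates ignore baseline.
- **That retention effort is confined to the intervention arm.** Data management {19} names that arm but does not say it is the only one, and {18b} covers everyone.

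**Conclusion.** The point holds as a contradiction with a real consequence. Two sections give opposite orders for consent and randomisation, and the order in Study implementation, read with open allocation and recruitment by ASHAs, permits entry that depends on the arm. The document shows a risk, not that bias will occur, and the risk cannot be quantified from what it gives. The conclusion rests on one inference, that ASHAs know their sub-centre's allocation once it is assigned, and on the absence of any stated concealment during recruitment. If the timeline's order is what was actually done, the recruitment problem disappears and only the text needs correcting. The uneven wording on retention is a secondary inconsistency.

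**What to change.** 1. Amend Study implementation to match the Participant timeline {13}. In all 18 sub-centres, complete listing, eligibility, consent and baseline before the statistician releases any allocation, and release all 18 together.
2. For any cluster already allocated, fix the eligible list from ENDIRA records dated before allocation. Report the numbers eligible, approached and consented, with baseline characteristics, by cluster and arm. Trial status expects the last inclusion in April 2026 and the article is dated June 2026, so this may be the only route left. It makes selection visible but does not undo it.
3. Reconcile Data management {19} with {18b}, so that reminders before the 6- and 12-month assessments are the same in both arms.

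The cost is a delay of some weeks in releasing allocation, within a 24-month study. The fallback adds recruitment logging, and the third item may add some contact in control clusters.
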